## Abstract

**Background:**

Given the scarce donor supply, an increasing number of so-called marginal or extended criteria donor (ECD) organs are used for liver transplantation. These ECD liver grafts are however known to be associated with a higher rate of early allograft dysfunction and primary non-function because of a greater vulnerability to ischemia–reperfusion injury. The end-ischemic hypothermic oxygenated machine perfusion (HOPE) technique may improve outcomes of liver transplantation with ECD grafts by decreasing reperfusion injury.

**Methods:**

HOPExt trial is a comparative open-label, multicenter, national, prospective, randomized, controlled study, in two parallel groups, using static cold storage, the gold standard procedure, as control. The trial will enroll adult patients on the transplant waiting list for liver failure or liver cirrhosis and/or liver malignancy requiring liver transplantation and receiving an ECD liver graft from a brain-dead donor. In the experimental group, ECD liver grafts will first undergo a classical static cold (4 °C) storage followed by a hypothermic oxygenated perfusion (HOPE) for a period of 1 to 4 h. The control group will consist of the classic static cold storage which is the gold standard procedure in liver transplantation. The primary objective of this trial is to study the efficacy of HOPE used before transplantation of ECD liver grafts from brain-dead donors in reducing postoperative early allograft dysfunction within the first 7 postoperative days compared to simple cold static storage.

**Discussion:**

We present in this protocol all study procedures in regard to the achievement of the HOPExt trial, to prevent biased analysis of trial outcomes and improve the transparency of the trial results. Enrollment of patients in the HOPExt trial has started on September 10, 2019, and is ongoing.

**Trial registration:**

ClinicalTrials.gov NCT03929523. Registered on April 29, 2019, before the start of inclusion.

**Supplementary Information:**

The online version contains supplementary material available at 10.1186/s13063-023-07402-0.

## Administrative information

Note: the numbers in curly brackets in this protocol refer to SPIRIT checklist item numbers. The order of the items has been modified to group similar items (see http://www.equator-network.org/reporting-guidelines/spirit-2013-statement-defining-standard-protocol-items-for-clinical-trials/).

Role of sponsor {5c}	The study sponsor and funder had no part in the study design, data collection, management, analysis, and interpretation of the data, writing of the report, and in the decision to submit the report for publication. They had no ultimate authority over any of these activities.

## Introduction

### Background and rationale {6a}

Ischemia–reperfusion (I/R) injury is universal in organ transplantation and results in microcirculatory and hepatocellular damage [1]. After liver transplantation, I/R leads to various degrees of graft dysfunction. Liver transplantation encompasses two forms of liver ischemia, namely cold and rewarming ischemia, both inducing hepatocellular injury. Cold ischemia occurs during organ retrieval, when the liver is cooled, perfused and then stored in a cold preservation solution. Rewarming ischemia is encountered during back-table graft preparation and also at the implementation stage while performing the vascular anastomoses before reperfusion [2]. Despite this fact, the preservation method for organ transplantation has been left unchanged for many years and simple static cold storage still remains the gold standard worldwide.

Given the scarce donor supply, an increasing number of so-called marginal or extended criteria donor (ECD) organs are used for liver transplantation, grafts which were previously rarely considered [3]. While there is no international consensus on the definition, ECD criteria include donor’s age over 65 years, donors in intensive care therapy for more than 7 days, obesity, fatty liver, prolonged cold ischemia time for over 12 h, and elevated liver enzymes or high natremia at any time in the donor. According to EuroTransplant and the French organ procurement organization (OPO) “Agence de la Biomédecine”, 40 to 50% of liver grafts are provided from ECD donors in Europe and in France, with the rate increasing over recent years (2016 report by the “Agence de la biomédecine”). These ECD liver grafts are however known to be associated with a higher rate of early allograft dysfunction (EAD) and primary non-function (PNF) because of a greater vulnerability to I/R injury. Although most authors agree that the graft function finally recovers, EAD is associated, in turn, with increased recipient susceptibility to sepsis [4], longer intensive care unit (ICU) and hospital stays [5–7], graft loss [8], and greater morbidity and mortality [9, 10].

Considering the excellent results achieved with machine perfusion preservation in kidney transplantation from ECD donors, machine perfusion techniques have been developed for liver grafts during the past decade and have shown promising results by decreasing reperfusion injury. Two major techniques for liver machine perfusion have been developed: normothermic or hypothermic oxygenated perfusion [11]. Normothermic liver perfusion with whole blood as perfusate requires an immediate start of normothermic perfusion at the place of organ procurement and during transport, as combination with previous cold storage has been shown to be disadvantageous [12]. Similarly, transportable cold perfusion devices for continuous cold perfusion after procurement require huge logistics and advanced technologies, not yet often available in routine clinical practice [13]. These continuous perfusion techniques have several drawbacks, including major logistical efforts and a risk of organ damage during perfusion and transport.

In contrast, the end-ischemic hypothermic oxygenated perfusion (HOPE) technique, which consists of using the machine perfusion procedure only during the last hours prior to transplantation, can be easily applied in the operating room where the transplant takes place, without any deviation from the usual organ transport and preparation methods used in the static cold storage procedure. Usually, during recipient hepatectomy, an interval of 1 to 3 h accumulates before the graft can be implanted. This period fits with the concept of a short-term hypothermic machine perfusion, applied after back-table preparation without delaying the transplant procedure. HOPE has been extensively tested in preclinical animal experimentations [14]. While the benefits of HOPE have been clinically demonstrated in donation after cardiac death (DCD) liver transplantations [15], there are sufficient arguments to hypothesize that the HOPE technique is superior to cold storage preservation of ECD liver grafts from brain-dead donors and may improve graft function and patient outcome after liver transplantation.

Despite the fact that liver machine perfusion is a promising method in liver transplantation, it has not spread into clinical practice as few results from randomized controlled trials (RCT) are currently available [16–18].

The HOPE technique appears to be simple and safe to perform because it is applied only a few hours before graft implantation in the transplantation center following usual transportation in static cold storage. Its feasibility and diffusion to teams are therefore easier.

### Objectives {7}

#### Primary objective

To assess the efficacy of HOPE, used before the transplantation of ECD liver grafts from brain-dead donors, in reducing postoperative early allograft dysfunction (EAD) within the first 7 postoperative days (POD) compared to simple cold static storage.

#### Secondary objectives

To assess the impact of HOPE on the following features compared to simple cold static storage:

Quality of conservationIschemia–reperfusion injuriesIntra-operative events (bleeding, post-reperfusion syndrome)Postoperative outcomes (liver function tests not included in the definition of EAD, kidney function tests)90-day morbidity and mortalityLength of hospital stay and intermediate care unit stayIntra- and extrahepatic biliary complications within the first year after liver transplantationMid-term outcome (3-month and 1-year patient survival and graft survival)Costs of liver transplantation with ECD graft using HOPE or not

To perform cost-effectiveness analysis.

## Trial design {8}

The HOPExt trial is a comparative open-label, multicenter, national, prospective, randomized, controlled, superiority study (1:1 ratio), in two parallel groups, with static cold storage as control.

## Methods: participants, interventions, and outcomes

### Study setting {9}

The study is conducted in eight transplantation centers located in University hospitals scattered throughout France. The list of participating centers is presented in Supplementary Material 1.

### Eligibility criteria {10}

Inclusion criteriaWritten informed consent prior to the performance of any study-specific procedureAffiliated to the French social security systemRecipient age ≥ 18 yearsPatient undergoing primary liver transplantationCandidate for a first elective liver transplantation, whatever the indicationTransplanted with a liver graft harvested from a brain-dead ECD defined as the presence of at least one of the following criteria:Donor age > 65 yearsIntensive care unit stay > 7 daysBMI > 30Proven biopsy macro-steatosis ≥ 30%Natremia > 155 mmol/L at any timeAST > 150 IU/L at any timeALT > 170 IU/L at any time

Non-inclusion criteriaFulminant hepatic failureRetransplantationSplit liver transplantationLiving donor liver transplantationGraft donated after cardiac arrest (DCD graft)Domino transplantationCombined liver transplantUnexpected medical contraindication to liver transplantationPatient participating in other interventional research, excluding routine care research (old regulation) and category 2 research not interfering with primary endpoint analysisPatient under legal protectionPatient deprived of liberty by a judicial or administrative decisionPatient refusing to participate in the studyPregnant or lactating womenInability to understand information concerning the protocol

### Who will take informed consent? {26a}

Patients will be informed during pre-transplantation consultations with a surgeon or a hepatologist prior to being placed on the waiting list for liver transplantation. For patients already on the waiting list, information could be made during a follow-up outpatient consultation. A time to think will be left to the patient. Once the patient has asked all questions concerning the study and agrees to participate in the study, consent will be signed by both the patient and the investigator.

Final inclusion and randomization will be done after accepting a liver graft that meets the ECD criteria.

### Additional consent provisions for collection and use of participant data and biological specimens {26b}

No additional studies that may use the data collected in this trial are planned.

## Interventions

### Explanation for the choice of comparators {6b}

The standard French liver allocation rules will be followed. The study does not interfere or change the process of accepting or declining a liver graft offered to a patient in any way. If the liver is suitable for transplantation and all inclusion and exclusion criteria are met, the liver will be randomized to either HOPE after cold storage or static cold storage only. The control group will use the gold standard static cold storage technique (4 °C) with Institute George Lopez (IGL-1)® solution from graft harvesting until liver transplantation as routine practice in the eight centers.

### Intervention description {11a}

#### Study group

##### Identification of the medical device

ECD liver grafts will be perfused with hypothermic oxygenated perfusion (HOPE) via the portal vein only for a minimum of 1 h (ideally 1–4 h) after the “back-table” phase (graft preparation). This will be performed, in parallel with the recipient hepatectomy, using the CE-certified Liver Assist® perfusion pump/device (XVivo®, Sweden) with Machine Perfusion Solution (Belzer-MPS, CE-certified). Ideally, the graft should be placed in the machine before or at the time of the incision of the recipient to allow a duration of machine perfusion of the graft between 1 and 4 h. The machine perfusion time should not exceed 4 h. However, if the hepatectomy phase is longer than expected, the graft can remain on perfusion and used for transplantation. A notification of adverse events with specific interest will have to be done if the hypothermic oxygenated perfusion lasted more than 4 h.

The Liver Assist® is a pump system providing temperature-controlled dual oxygenated isolated perfusion of donor livers to bridge the time span between the donor hepatectomy and the liver transplantation in the recipient.

The Liver Assist® is a modular system consisting of five main modules:Portal vein pump unit (for portal vein perfusion)Hepatic artery pump unit (for hepatic artery perfusion) (*not used in this study* where only the portal vein is perfused) Thermo unitTrolley including table topDisposable set

The device incorporates neither medical substances nor non-viable materials of animal origin.

Date of CE mark: CE 663647 25/11/2016.

Market authorization: November 29, 2006.

#####  Intended use of the medical device

The Liver Assist is intended to be used for isolated ex vivo oxygenated machine perfusion of donor livers, for up to a period of 4 h.

##### Method of use of the device

If the patient is randomized into the machine perfusion group, the first part of graft preservation is similar to the control group. The graft is perfused and stored in Institute George Lopez (IGL-1®) solution at 4 °C during transport to the transplantation center.

As soon as the liver graft arrives at the transplantation center, the surgeon immediately prepares it on the back-table. The graft is then put on the Liver Assist perfusion machine around the time the transplant procedure begins.

Perfusion settings will be:Use of the same perfusion machine device in all centers (Liver Assist, Xvivo)Hypothermic perfusion (8–12 °C)Portal vein perfusion: portal vein is cannulatedAdjusted perfusion flow: 150–250 ml/min under 3 mmHg in the portal veinPerfusate oxygenation at 70 kPAUse of 3 L of perfusion solution: Machine Perfusion Solution (Belzer-MPS, Bridge-To-Life, CE-certified)

##### Contraindications, warnings, possible risks

The Liver Assist perfusion machine is routinely used worldwide, and many experiments in patients have been reported in the literature [14]. There are no specific contraindications. The main advantage of hypothermic perfusion compared to normothermic perfusion, is that, in the event of a defect in the machine, the liver graft stays in hypothermic conditions and is protected against ischemic injuries. Even if the machine cannot be run, the liver graft is kept in static cold storage and can still be implanted in the recipient.

#### Control group

The control group will use the gold standard static cold storage technique (4 °C) with Institute George Lopez (IGL-1)® solution from graft harvesting until liver transplantation as routine practice in the eight centers.

### Criteria for discontinuing or modifying allocated interventions {11b}

In the following instances, patients will terminate the study prematurely if:Technical problem preventing any use of the perfusion machineNon-transplantable patients (e.g., peritoneal carcinosis)

However, all patients undergoing liver transplantation under the protocol conditions will be included in the modified intention-to-treat analysis (full analysis set).

### Strategies to improve adherence to interventions {11c}

The intervention is a single event requiring no adherence monitoring.

### Relevant concomitant care permitted or prohibited during the trial {11d}

There are no additional restrictions other than those listed in the non-inclusion criteria.

### Provisions for post-trial care {30}

The sponsor has subscribed to an insurance policy for the entire duration of the study, covering its own civil liability as well as that of all the physicians involved in the realization of the study. It will also insure the full compensation for harmful consequences of the research for the participating persons and their beneficiaries, except with evidence, at their responsibility, that the damage is not attributable to their mistake or to that of all consultants, without the possibility of being opposed to an act by a third party or the voluntary withdrawal of the person who had initially consented to participate in the research.

### Outcomes {12}

#### Primary endpoint

Difference between the two treatment arms in the proportion of patients with early allograft dysfunction (EAD). EAD (according to Olthoff et al. [7]) is defined by the presence of at least one of the following criteria:Bilirubin level > 10 mg/dL (i.e., 171 μmol/L) on postoperative day (POD) 7INR > 1.6 on POD 7AST or ALT level > 2000 IU/L within the first 7 PODs

Primary non-function (PNF) of the graft is the very last stage of any EAD and is defined by the presence of at least one of the following criteria:Graft loss within the first 7 PODsPatient’s death within the first 7 PODs

#### Secondary endpoints

Quality of conservationDosage during perfusion by the HOPE machine (AST, ALT, LDH, hyaluronic acid, lactate levels in machine perfusate at 30 min and at the end of the perfusion)Additional 3 mL of machine perfusate will be sampled at 30 min and at the end of machine perfusion and stored at − 80 °C. Those samples will be used in case of future unexpected research about machine perfusate compoundsDifference between the two treatment arms in the proportion of patients with ischemia–reperfusion injuriesLiver injury assessed by serum AST and ALT at 6 h (± 2 h), 12 h (± 2 h) and every day until POD7 after transplantationPost-reperfusion liver biopsy (histological changes, level of necrosis)Untargeted liver graft metabolic profiling (by high-resolution nuclear magnetic resonance—1H HR-NMR spectrometer) on liver biopsies on the back-table in both study groups and immediately after liver perfusion in the HOPE group. This test will be centralized in the Strasbourg centerDifference between the two treatment arms in the proportion of patients with intra-operative eventsIntra-operative blood transfusions (red blood cells, fresh frozen plasma, thrombocyte concentrate)Occurrence of post-reperfusion syndrome, defined as a 50% decrease in median arterial pressure during the 5 min following the graft revascularizationDuration of surgery Postoperative outcome (liver function tests not included in the definition of EAD)Difference in means between the two treatment arms for:
Recipient blood level of factor V at 6 h (± 2 h), 12 h (± 2 h) and every day until POD7Arterial lactates at 6 h (± 2 h), 12 h (± 2 h) and every day until discharge from intensive care (and maximum until POD7)MEAF score (0–10) at POD3, including POD3 bilirubin, ALT max, and INR max at POD3. This score will be compared with the Olthoff’s definition of EAD and the L-GrAFT risk factorL-GrAFT risk factor (− 6 to + 6) including AST, INR, total bilirubin, and platelets every day until POD 10. This score will be compared with both MEAF score and Olthoff’s scoreKidney function testsDaily serum creatinine level during the first 7 PODsDaily glomerular filtration rate (assessed using MDRD and CKD-EPI) during the first 7 PODsDifference between the two treatment arms in the proportion of patients requiring renal dialysis within the first 7 PODs90-day morbidity and mortalityDifference between the two treatment arms in the proportion of patients with severe postoperative complication (defined as Dindo–Clavien classification ≥ 3) occurring before day 90 post surgeryDifference in means between the two treatment arms of the comprehensive complication index (CCI) [19] at day 90Difference between the two treatment arms in the proportion of patients who were deceased before day 90 after surgeryDifference in means between the two treatment arms of the length of intermediate care unit stay and total hospital stayDifference between the two treatment arms in the proportion of patients with intra- and extrahepatic biliary complications within the first year after liver transplantation, assessed by:Serum cholestasis parameter (bilirubin, gamma*-*glutamyl transferase, alkaline phosphatase) every 3 months until 1 yearLiver contrast-enhanced MRI, including a magnetic resonance cholangiopancreatography (MRCP), 12 months after liver transplantation (except for patients who underwent a re-transplantation during the study)Actuarial graft and patient’s survival rates at 3 months and 1 yearDifference between the two treatment arms in the proportion of patients without graft loss at 3 months and 1 year.Difference between the two treatment arms in the proportion of patients alive at 3 months and 1 year.Costs of liver transplantation with ECD grafts using HOPE or not, incremental cost-effectiveness ratio at 12 months post-surgery. Details about the cost-effectiveness analysis are given in Supplementary Material 2.

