#### Conduct of the study

The overall schedule and time commitment for trial participants are summarized in Table 1.

**Table 1 Tab1:** Schedule of enrolment, interventions, and assessments in the HOPExt trial

Stages	V1 screening	V2 inclusion		V3	V4	V5–V11	V12	V13–V16
Time point	At inscription for LT or at pre-LT visit	D0 At hospitalization for LT	D0 HOPE group only	D0 + 6h (+/-2h) after LT	D0 + 12h (+/-2h) after LT	Day 1 to day 7 (+/-1day)	End of hospital stay	M3; M6: M9 and M12 (+/-30 days)
Actions								
Inclusion/non-inclusion criteria	X	X						
Informed consent	X							
Medical history and patient characteristics^1^	X							
MELD score	X At inscription	X						
Randomization^2^		X						
Clinical examination^3^		X					X	X
Biological analyses^4^		X (before LT)		X	X	X	X	X
Child–Pugh score		X (before LT)						
Donor characteristics^5^		X						
HOPE perfusion parameters^6^			X					
Bacteriological and fungal analyses^7^		X	X					
Intra-operative data^8^		X						
Liver biopsy^9^		X both groups	X					
Machine perfusate sample^10^			X					
ICU and hospital stay							X	
Morbidity (Clavien–Dindo score, CCI)							X	X At M3 only
Concomitant medication		X		X	X	X	X	X
Adverse events		X		X	X	X	X	X
Abdominal contrast enhanced MRI/MRCP								X At M12 only

^1^Patient characteristics: age, gender, height, weight, BMI, blood group, cause of cirrhosis, indication for transplantation, medical history (diabetes mellitus, arterial hypertension, transjugular intrahepatic portosystemic shunt), pretransplant status of residence (home, hospital ward or intensive care unit (ICU))

^2^Randomization will be performed after the harvesting team has macroscopically assessed the graft and confirmed that the graft will be harvested. After checking the inclusion and non-inclusion criteria, an online randomization tool will be used. Randomization will be stratified by center and MELD score at the time of transplantation with a cut-off of 30

^3^Clinical examination: vital signs (temperature, blood pressure, heart rate), body weight, height, BMI

^4^Biological analyses: AST, ALT, GGT, alkaline phosphatase, bilirubin, factor V, INR, platelets, creatinine, GFR, lactates. At V2 only, a pregnancy test (beta HCG) will be done for women of childbearing age

^5^Donor characteristics**:** age, gender, height, weight, BMI, blood group, length of stay in intensive care unit, cause of death, occurrence of cardiac arrest, biological test (AST, ALT, natremia)

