#### Follow-up visits

Visits 3–11 (6 and 12 h (± 2 h) after reperfusion and postoperative days 1–7, ± 1 day):Laboratory analyses (AST, ALT, GGT, alkaline phosphatase, bilirubin, factor V, INR, platelets, creatinine, GFR, lactates) will be performed. Concomitant medications and adverse events will be collected.

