#### Visit 12 (last day of hospitalization)

Physical examination and laboratory analyses (AST, ALT, GGT, alkaline phosphatase, bilirubin, factor V, INR, platelets, creatinine, GFR, lactates) will be performed. Immunosuppression medication will be confirmed and post-transplant complications (Clavien–Dindo Score, CCI) will be assessed. Concomitant medications and adverse events will be collected. Post-transplant ICU and hospital stay will be assessed.

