#### Visit 13 (3 months (± 30 days))

After liver transplantation, patients have regular checks at hospital, where physical examinations and lab test are performed (AST, ALT, GGT, alkaline phosphatase, bilirubin, factor V, INR, platelets, creatinine, GFR). During this appointment, the following will be recorded: the incidence of main postoperative complications (kidney function disorders, need for dialysis, infections, cholestasis and biliary obstructions, vascular complications, acute rejection, arterial or portal vein thrombosis, biliary fistula), Clavien–Dindo classification score, comprehensive complication index (CCI), reintervention, length of stay in intensive care unit, length of hospital stay, retransplantation, or death within 3 months after liver transplantation.

Adverse events and concomitant medications will be collected.

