### Data management {19}

Patient data needed for the study will be collected in an e-CRF. This e-CRF, developed via the Ennov Clinical software, will be specific to the study.

The patient code (see the paragraph “Confidentiality {27}”) will be the only information on the e-CRF which will link the data to the patient.

The e-CRF will only include the data needed to analyze the efficacy and safety of patients and for publication (information required by the protocol). Other data relating to the patient and necessary for their follow-up outside the study will be collected in their medical file. An explanation will be provided for each missing data.

At the end of the study, a paper print will be requested, which must be authenticated (dated and signed) by the investigator. A copy of the authenticated document for the sponsor must be archived by the investigator.

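### The L-GrAFT secondary endpoint calls for daily laboratory values to POD 10, but the visit schedule provides them only to POD 7, so two or three of the ten days are unscheduled for each patient

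*Protocol article*

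**What the plan says.** Under Outcomes {12}, Secondary endpoints, L-GrAFT is listed among the postoperative measures whose means are to be compared between arms. It is described as "including AST, INR, total bilirubin, and platelets every day until POD 10". The same item says that it will also be compared with the MEAF score and with the Olthoff definition of EAD.

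The laboratory schedule appears in two places, and they agree with each other. In Table 1 (Conduct of the study) the column for V5–V11 reads "Day 1 to day 7 (+/-1day". The Follow-up visits section reads "Visits 3–11 (6 and 12 h (± 2 h) after reperfusion and postoperative days 1–7, ± 1 day". The next laboratory panel is at visit 12, on the last day of hospitalization: "Physical examination and laboratory analyses (AST, ALT, GGT, alkaline phosphatase, bilirubin, factor V, INR, platelets, creatinine, GFR, lactates) will be performed". After that comes visit 13, at 3 months ± 30 days.

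Footnote 4 of Table 1 gives the panel: "Biological analyses: AST, ALT, GGT, alkaline phosphatase, bilirubin, factor V, INR, platelets, creatinine, GFR, lactates". All four L-GrAFT analytes are in it, so the shortfall is in days and not in tests.

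Data management {19} limits what is recorded: "The e-CRF will only include the data needed to analyze the efficacy and safety of patients and for publication (information required by the protocol". For missing secondary-endpoint data, section {20c} leaves the choice between treating values as missing and imputing them to the principal investigator and the person in charge of the analysis.

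**The concern.** The definition asks for a daily series that runs three days beyond the last scheduled daily visit. The neighbouring early laboratory endpoints with a stated daily series (AST and ALT, factor V, lactates, creatinine, glomerular filtration rate) stop at POD 7 or sooner and match the schedule. L-GrAFT is the only one that outruns it, which suggests an oversight.

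Two things are at stake. First, a named between-arm endpoint, and its planned comparison with two other definitions of graft dysfunction, would rest on an incomplete series if sites follow the schedule. Second, if the gap is filled from routine inpatient results, longer stays yield more complete series. The Background {6a} says that EAD is associated with longer hospital stays, and length of stay is itself a secondary endpoint. Completeness of the score could then be related to what the score measures, and to arm if HOPE works. The protocol fixes no rule for this gap, although it can be foreseen.

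An analysis plan can say how to handle missing values. It cannot supply values that no visit collects.

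**Working it through.** The protocol gives no figure of its own for this point, so the check sets the required days against the scheduled days.

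**Inputs**
- Required: four analytes daily to POD 10 (Secondary endpoints). The starting day is not stated; POD 1 is assumed, which gives 10 days.
- Scheduled daily: POD 1 to 7, seven visits, window ± 1 day (Table 1; Follow-up visits).
- Scheduled once: visit 12, on the last hospital day, which varies by patient.
- Next after that: month 3.

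**Step 1: daily visits only.** Required {1,…,10} minus scheduled {1,…,7} leaves {8, 9, 10}. That is 3 of 10 days, or 3 × 4 = 12 of 10 × 4 = 40 analyte-days.

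**Step 2: add visit 12.**

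| Visit 12 falls on | Days still unscheduled | Count |
|---|---|---|
| POD 7 or earlier | 8, 9, 10 | 3 of 10 |
| POD 8 | 9, 10 | 2 of 10 |
| POD 9 | 8, 10 | 2 of 10 |
| POD 10 | 8, 9 | 2 of 10 |
| after POD 10 | 8, 9, 10 | 3 of 10 |

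Each patient therefore has at least two unscheduled days (2 × 4 = 8 of 40 analyte-days) and otherwise three.

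**Step 3: does the ± 1 day window close the gap?** It can move the POD 7 visit to POD 8. Seven visits still give at most seven daily values, and visit 12 adds at most one: 7 + 1 = 8 of 10.

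**Step 4: does the starting day matter?** If the series were counted from POD 0, with the 6 h and 12 h draws covering that day, 11 days would be required and 8 covered by daily visits. The same three days remain open.

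**Step 5: what else is touched?** The EAD criteria use POD 7 values and transaminases within the first 7 days, and MEAF uses POD 3. Both lie inside the schedule. The sample size rests on EAD (30% versus 15%). With the arcsine effect size h = 0.3639, n = 2 × ((1.960 + 0.842)/h)² = 118.6, so 119 per group, which is the stated figure. Nothing here changes it.

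**The case against.** The strongest reply is that the endpoint definition is itself protocol text. If the e-CRF holds what the protocol requires, POD 8 to 10 values belong in it. The form is in a supplement that is not shown, Table 1 is described as a summary, and the article condenses a longer protocol. Patients still in hospital may well have routine results on those days. This stands to the extent that the document does not prove the values go uncollected. It does not remove the contradiction: the article prints a full schedule and a visit-by-visit narrative, both stop at POD 7, and a site following them has no instruction to record POD 8 to 10. Nor would routine results give a full daily series for patients discharged before POD 10.

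Three stronger readings are tempting and are not supported.
- A reader might infer that 30% of the score is lost in every randomized patient. Visit 12 can supply one of the three days. The 30% is also a count of days: the document gives no formula for the score, so the effect on its value is unknown.
- A reader might infer that POD 8 to 10 values would exist only for patients whose last hospital day falls then. That holds for scheduled draws only; routine results may exist for anyone still in hospital.
- A reader might infer that the arm comparison is biased. The document gives no length-of-stay figures, so neither the size nor the direction of any bias can be stated.

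**Conclusion.** The contradiction is real and lies within the document. If only the scheduled visits are used, L-GrAFT cannot be computed as defined: two or three of the ten daily values per analyte are unscheduled for each patient, depending on whether visit 12 falls on POD 8, 9 or 10. This assumes counting from POD 1 and a schedule as printed in Table 1 and the visit text.

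Whether the values are in fact recorded depends on an e-CRF that is not shown. If they come from routine inpatient results, completeness follows discharge date, and the document's own background gives reason to expect that to be related to graft function. That is a plausible route to selective missingness, not a demonstrated bias.

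The reach is limited to one secondary endpoint and its comparison with MEAF and the Olthoff definition. It should be corrected, but it does not threaten the trial's main conclusion.

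**What to change.** Amend the L-GrAFT item in Outcomes {12}, Table 1 and the Follow-up visits text together, in one of two ways.

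1. **Keep the POD 10 definition.** Add e-CRF fields for the four analytes on POD 8, 9 and 10, filled from results already measured in inpatients. State one rule, applied identically in both arms, for patients discharged before POD 10, and fix it before outcomes are compared by arm. The cost is at most 3 × 4 = 12 transcribed values per patient and no extra procedure. For patients already past POD 10, the values would have to be taken from the charts.
2. **Redefine the endpoint on the POD 1 to 7 data that are collected, and label it as such.** The cost is a wording change, and a score that differs from the POD 10 version and should not be reported under the same name without that qualification.

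The first option keeps the endpoint as defined but leaves a rule to be written for early discharge. The second avoids dependence on discharge after POD 7 but changes the score.
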